#### Analysis of count data (ventilator‐free days, hospital/institution‐free days, and mRS (ordinal score))

2.12.4

We will present count data as means, mean differences, and 95% confidence intervals or medians, interquartile ranges, and 95% confidence intervals (bootstrapping) depending on the observed distribution. We will analyze count data using the stratified Wilcoxon test stratified for the other interventions.

We will present mock tables for the three comparisons separately in each protocol. This includes baseline tables, results tables, survival curves, and graphs/tests illustrating separation between the groups (sedation, temperature, and MAP).

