### Randomization and blinding

2.3

Trial sites will have access to an internet‐based application for immediate randomization to ensure adequate allocation concealment and sequence generation. Each patient will be assigned to three trials simultaneously. Randomization will be performed with permuted blocks of varying size, stratified for trial site only. Investigators will be blinded to the block sizes. The team treating the patient (physicians, nurses, and others) will not be blinded to the allocation group due to the inherent difficulty in blinding the interventions (sedation, temperature, and arterial pressure). Measures will be taken to ensure that the information about allocation will not be disseminated beyond the immediate group of caregivers responsible for patient care. The clinicians performing neuroprognostication, outcome assessors, statisticians, data managers, steering group, and manuscript writers will be blinded to treatment allocation.

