### General analysis principles

2.11

We will conduct all analyses according to the intention‐to‐treat principle (ITT), that is, all randomized participants with available data will be included in all analyses.

We will assess if the statistical and clinical significance thresholds are crossed (Bayes factor calculations will be reported in supplementary material).^17^ Assessment of clinical significance will be based on the anticipated intervention effects used in the sample size and power estimations.^17^ Our primary conclusion will be based on the primary outcome, so all tests of statistical significance (including subgroup analyses) will be two‐sided with a threshold of 5%.^17^ No conclusions will be drawn based on secondary outcomes.

It is generally acknowledged that regression analyses ought to be adjusted for the stratification variables used in the randomization.^18^, ^19^, ^20^ Hence, when analyzing each of the three trials, we will adjust all analyses for ‘site’ and the allocated intervention in the two other trials (e.g., the SED‐CARE outcomes will be adjusted for ‘site’ and the allocated TEMP‐CARE and MAP‐CARE interventions). We will assess whether there are significant interactions between trial interventions (for details, see Section 2.14).

We will perform the following subgroup analyses:Age (higher or lower than the median)Sex (male/female)Cardiopulmonary resuscitation by bystander (yes/no)Initial rhythm (shockable vs. non‐shockable)Time to ROSC (higher or lower than the median)Circulatory status on admission (presence or absence of circulatory shock diagnosed by the treating physician)Baseline risk of poor neurologic outcome (Miracle2‐score: low risk (0–2), medium (3–5), and high (6–10).^21^)Presumed cause of arrest at randomization (cardiac vs. others)Chronic hypertension as a comorbidity

We plan to reanalyze all three trials using Bayesian statistics. Separate statistical analysis plans will be published.

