#### Analysis of continuous data

2.12.3

We will present continuous outcomes as means and standard deviations for each group, along with 95% confidence intervals for the means of the groups and the mean differences between the groups. We will analyze continuous outcomes using mixed effects linear regression with ‘site’ as a random intercept using an exchangeable covariance matrix, and we will include the allocated intervention in the two other trials as fixed effects. We expect that a large proportion of the participants will die before the assessment of HRQoL. When assessing health‐related HRQoL, we will, therefore, in a secondary analysis, impute a ‘0’ for all participants who died. We will analyze these data using the stratified Wilcoxon test stratified for the other interventions.

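### The stratified Wilcoxon tests omit site, although Section 2.11 promises site adjustment in all analyses; and at the planned mortality the median option for ordinal mRS cannot show the planned effect (minor)

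*SAP article*

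**What the plan says.** Section 2.3 says that randomisation is "stratified for trial site only". Section 2.11 gives a reason, that "regression analyses ought to be adjusted for the stratification variables used in the randomization", and then a commitment: "we will adjust all analyses for ‘site’ and the allocated intervention in the two other trials".

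The regression models keep to this. Sections 2.12.2 and 2.12.3 include site as a random intercept and the other two allocations as fixed effects.

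The rank tests do not. Section 2.12.3, on EQ-VAS with deaths set to 0, says: "We will analyze these data using the stratified Wilcoxon test stratified for the other interventions". Section 2.12.4, whose heading covers ventilator-free days, hospital/institution-free days and ordinal mRS, says: "We will analyze count data using the stratified Wilcoxon test stratified for the other interventions".

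For the same three outcomes, Section 2.12.4 offers two presentations: means with mean differences and confidence intervals, or "medians, interquartile ranges, and 95% confidence intervals (bootstrapping) depending on the observed distribution". It names no effect measure that corresponds to the Wilcoxon test.

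**The concern.** The rank tests condition on two factors that were not randomisation strata and drop the one that was. When allocation is balanced within site, differences between sites cancel out of the treatment comparison. A test that ignores site still counts them as noise, so its standard error is too large.

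There is also a practical problem. Section 2.15 has two statisticians analyse the data independently. One who follows Section 2.11 and one who follows Section 2.12.4 would obtain different p-values, and the steering group would have to choose between them.

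The second matter is what the reader sees beside the p-value for mRS. Death is mRS 6, and the plan expects more than half of each arm to die. If the median option is chosen, both medians sit at the death value and the summary cannot show the effect that the trial was designed to detect.

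**Working it through.** **Inputs from the SAP article, Section 2.10.** Mortality 60% versus 54.4%; 5% type I error (two-sided, Section 2.11); 90% power; 3278 participants before inflation; 3500 recruited; 1.8% loss. Equal allocation is assumed, giving 1750 per arm, or 3500 × 0.982 / 2 ≈ 1718 after losses.

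**Reproducing the plan's figure.** n per arm = [1.960·√(2 × 0.572 × 0.428) + 1.2816·√(0.60 × 0.40 + 0.544 × 0.456)]² / 0.056² = (1.3715 + 0.8953)² / 0.003136 ≈ 1638.5. This rounds up to 1639 per arm and 3278 in total, as stated.

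**Effect of leaving out site.** If site explains a share ρ of the outcome variance and arms are balanced within site, the test that ignores site overstates its variance by 1/(1 − ρ). Its true two-sided level is P(|Z| > 1.960/√(1 − ρ)). The documents give no ρ, so a range is assumed:

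| Assumed ρ | Variance overstated by | Effective cut-off | True level |
|---|---|---|---|
| 2% | 1/0.98 = 1.02 | 1.980 | 4.8% |
| 5% | 1/0.95 = 1.05 | 2.011 | 4.4% |
| 10% | 1/0.90 = 1.11 | 2.066 | 3.9% |

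A simulation of the stratified Wilcoxon (van Elteren) test gives the same picture. It assumed 3500 participants, 60 sites, blocks of 8 within site and an illustrative mRS distribution; only the 3500 is in the SAP. There were 500 null and 300 alternative runs per setting.

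| Site SD (log-odds) | Type I: other allocations / site / crossed | Power: other allocations / site / crossed |
|---|---|---|
| 0 | 5.4 / 5.6 / 6.0% | 94.3 / 94.3 / 93.7% |
| 0.3 | 5.4 / 6.0 / 5.6% | 93.0 / 94.0 / 92.7% |
| 0.5 | 3.8 / 4.6 / 5.0% | 93.0 / 93.0 / 92.7% |
| 0.8 | 3.8 / 5.4 / 5.4% | 94.7 / 97.3 / 96.3% |

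The Monte Carlo standard error of a 5% rate over 500 runs is √(0.05 × 0.95 / 500) ≈ 1.0 point, so the single cells are rough. A visible power loss appears only at the largest assumed SD.

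**Median mRS.** The median is 6 when more than half of an arm has died. At 54.4% and 1750 per arm, z = 0.044 / √(0.544 × 0.456 / 1750) = 0.044 / 0.0119 ≈ 3.70. The exact binomial probability of a median of 6 is 0.9999; at 60% mortality it is essentially 1. Both medians were 6 in 2000 of 2000 simulated trials.

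This depends on the mortality level. For the intervention arm at 1750:

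| Mortality | RR vs 60% | P(median = 6) |
|---|---|---|
| 54.4% | 0.91 | 0.9999 |
| 52% | 0.87 | 0.95 |
| 51% | 0.85 | 0.79 |
| 50% | 0.83 | 0.49 |
| 49% | 0.82 | 0.19 |
| 48% | 0.80 | 0.04 |
| 45% | 0.75 | about 0 |

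**Bootstrap interval.** The interval for an arm's median reaches below 6 roughly when observed mortality is under 0.5 + 1.96 × 0.5/√1718 = 0.5236. At true mortality 54.4% the chance is P(Z < (0.5236 − 0.544)/0.0120) = P(Z < −1.69) ≈ 4.5%.

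**What a matched measure would show.** Counting only death against survival, the probability that an intervention patient fares better, with ties halved, is 0.456 × 0.60 + ½(0.544 × 0.60 + 0.456 × 0.40) = 0.2736 + 0.2544 = 0.528, against 0.5 for no effect. The odds ratio for death is (0.544/0.456)/(0.60/0.40) = 0.80. Both express the planned effect where the medians do not.

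**The case against.** The strongest reply is that almost nothing depends on this. The tests concern three exploratory outcomes and one secondary analysis of a secondary outcome; Section 2.11 draws no conclusions from secondary outcomes; and the main EQ-VAS analysis already carries a site intercept. Omitting site errs on the safe side. All of this stands, and it is why the point is minor. One might add that the reason in Section 2.11 speaks of regression and that a rank test takes no random intercept. But the commitment that follows covers all analyses, and a Wilcoxon test can be stratified by site.

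Several stronger readings are tempting, and the document does not support them:

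- A reader might infer that the medians will be 6 versus 6 whatever the effect. They separate once one arm falls to about 50% mortality or below, a reduction of some 10 points against the planned 5.6.
- A reader might infer that medians are the planned summary. Means with mean differences are an equal option in Section 2.12.4 and would move: 4.34 versus 4.06 in an illustrative distribution matching 60% dead and 65% poor outcome against 54.4% and 58.5%. They do assume equal spacing of mRS steps.
- A reader might extend the median problem to EQ-VAS with deaths set to 0. Section 2.12.3 presents continuous outcomes as means, so this does not follow.
- A reader might expect a zero-width interval for a median difference. A degenerate interval is likely at the planned rates but not certain, and the plan attaches a difference only to means.
- A reader might infer that the mRS distribution by arm will not be reported. The results tables are left to the protocols, which are not shown.

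Replacing every rank test by a proportional-odds model is a matter of preference and adds an assumption. Labelling mRS as count data is loose wording; a rank test suits an ordinal score.

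**Conclusion.** The inconsistency is real: Section 2.11 promises site adjustment in all analyses, and the Wilcoxon sentences in Sections 2.12.3 and 2.12.4 leave site out without an exception. The cost is mild conservatism, with a true level of roughly 3.9% to 4.8% for an assumed site share of 10% down to 2%, and a power loss of about 2 to 3 points at the most extreme site variation simulated and hardly any below it. These sizes rest on a between-site variation that the document does not give. Type I error is not inflated, and the primary outcome is unaffected.

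The median option for ordinal mRS is uninformative at the plan's own 60% versus 54.4% mortality, and would remain so while mortality stays clearly above 50% in both arms. Severity: minor.

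**What to change.** 1. In Sections 2.12.3 and 2.12.4, stratify the Wilcoxon tests by site as well as by the other two allocations, or by site alone if the crossed strata become too small, and write down beforehand what counts as too small. A site with 30 participants, the planned minimum in Section 2.14.1, would have about 30/4 = 7.5 per crossed stratum. In the simulation, site alone did at least as well as the crossed strata on power. The pooling of small sites foreseen in Section 2.14.1 can serve here too.
2. For ordinal mRS, drop the median option. Report the distribution by arm and one effect measure that matches the rank test, with its 95% CI: for example the probability of a better outcome, or a common odds ratio from a model with a site term. The odds ratio is an average effect if the odds are not proportional. If the protocols' mock tables already show the distribution, a reference to them is enough.

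Both are wording changes made before analysis. They need no new data and leave the sample size and the primary analysis as they are.

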### Handling of missing data

2.13

In the primary analysis we will include all randomized participants with available data (please see the Section 2.12.3). We will handle missing data according to the recommendation by Jakobsen et al.^22^ In short, we anticipate that the proportion of missing values on main dichotomous outcomes will be less than 5%. We will consider using multiple imputations and present best‐worst and worst‐best case scenarios if it is not valid to ignore missing data.^22^ Best‐worst and worst‐best case scenarios assess the potential range of impact of the missing data for the trial results.^22^ In the best‐worst case scenario, it is assumed that all patients lost to follow‐up in the experimental group had a beneficial outcome (survived, had no poor functional outcome, etc.), and all those with missing outcomes in the control group had a harmful outcome (did not survive, had poor functional outcome, etc.).^22^ Conversely, in the worst‐best case scenario, it is assumed that all patients who were lost to follow‐up in the experimental group had a harmful outcome and that all those lost to follow‐up in the control group had a beneficial outcome.^22^ When continuous outcomes are used, we will define a beneficial outcome as the group mean plus two SDs of the group mean (fixed imputation), and a harmful outcome as the group mean minus two SDs of the group mean (fixed imputation).^22^

We will perform sensitivity analyses assuming that all participants with missing data were either all alive or dead.

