### Outcomes

2.8

The primary assessment time point will be 6 months after randomization for all outcomes. The outcomes are defined as primary, secondary, and exploratory. The sample size is based on the primary outcome, and our primary conclusions will be based on the results of the primary outcome.

Primary outcomeAll‐cause mortality

Secondary outcomesProportion of participants with a poor functional outcome measured at 6 months after randomization in either one of two ways (hierarchical order):Using the modified Rankin Scale (mRS) with mRS 4–6 indicating a poor outcome (dichotomized)OR if a mRS score cannot be assigned using the standardized assessment, a poor outcome (yes/no) will be based on whether the patient is dependent on others for basic activities of daily living (moving indoors, eating, dressing, personal hygiene)
Proportion of patients with a predefined serious adverse event in the index intensive care stay (defined differently for each trial):In *SED‐CARE*: death, sepsis or septic shock (Sepsis‐3 criteria),^6^ arrhythmia requiring defibrillation, cardioversion or chest compressions, venous thromboembolism, reintubation, or unplanned extubationIn *TEMP‐CARE*: death, sepsis or septic shock (Sepsis‐3 criteria),^6^ arrhythmia requiring defibrillation, cardioversion or chest compressions, venous thromboembolism, moderate or severe bleeding (GUSTO criteria)^7^
In *MAP‐CARE*: death, arrhythmia requiring defibrillation, cardioversion, or chest compressions, moderate or severe bleeding (GUSTO criteria),^7^ acute kidney injury with renal replacement therapy, limb ischemia requiring radiological or surgical intervention, or gut ischemia demonstrated at laparotomy/laparoscopy or clinically suspected based on abdominal CT‐scan
Patient‐reported Health‐Related Quality of Life (HRQoL) using EQ‐5D‐5L measured by EQ‐VAS.^8^

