### Sample size and power estimations

2.10

Based on the results of the TTM trial, TTM2 trial, and information from the International Cardiac Arrest Registry (INTCAR),^9^ we estimate that within 6 months after randomization, approximately 60% of the participants will die. We hypothesize that 6 months after randomization, 54.4% of the participants will die in the intervention groups, corresponding to a relative risk reduction of 9% (relative risk, RR = 0.91). With an acceptable risk of type‐1 error of 5% and an acceptable risk of type‐2 error of 10% (power of 90%), a total of 3278 participants (1639 in each pairwise comparison) would be required.

We plan to investigate the possible effects of adjustment for site and possible interactions between interventions using simulations.^10^ Preliminary simulations suggest that if there are interactions between the trial interventions on outcomes, it would be necessary to increase the sample size. The STEPCARE trial is being conducted with the assumption that there will be no such interactions between the trial interventions on outcomes. However, to accommodate the possibility of minor interactions, an increase in the sample size (5%) has been chosen to account for this. The combined effect of withdrawn consent and missing data on the primary outcome in the TTM2 trial resulted in a sample size reduction of approximately 2%. We assume a similar result in the current trial (1.8%). Considering the above‐mentioned factors, we will increase the sample size by 6.8% and recruit a total of 3500 participants.

We estimated the statistical power of all secondary outcomes.^11^ With an estimated sample size of 3500 participants in total, the functional outcome measure (dichotomized mRS) has a power of 98% to detect a relative risk of 0.90 for a poor functional outcome (mRS 4–6) in the experimental group, with 65% of cases in the control group experiencing a poor functional outcome.

For the predefined serious adverse events, we performed simulations to assess the incidences for the three serious adverse event outcomes. We had estimated incidences for arrhythmia, sepsis, and bleeding, but not for unplanned extubation, reintubation, and venous thromboembolism.^12^, ^13^ We also considered aggregate data from previous meta‐analyses and trials, and these numbers roughly corresponded to the simulations:^3^, ^4^, ^14^, ^15^, ^16^

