#### Outcomes

2.12.1

We will analyze the primary outcome as a binary variable (alive or dead). We will analyze the secondary outcomes as follows: (I) We will evaluate the functional outcome by dichotomizing the modified Rankin scale (0–3 vs. 4–6), or if this is missing, dependent versus independent in basic activities of daily life (moving indoors, eating, dressing, personal hygiene). (II) We will analyze serious adverse events as a binary variable (one or more versus no serious adverse event). Additionally, we will present each specific serious adverse event separately by risk ratios and 95% confidence intervals. (III) We will analyze HRQoL by EQ‐VAS scale as a continuous variable (0–100).

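### Functional outcome: the available-case rule drops known survivors without an assessment but keeps every known death as poor, so the reported poor-outcome proportions are probably somewhat too high

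*SAP article*

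**What the plan says.** **Analysis set.** The general principle in Section 2.11 is that "all randomized participants with available data will be included in all analyses". Section 2.13 repeats it: "In the primary analysis we will include all randomized participants with available data".

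**Outcome definition.** Section 2.8 defines a poor functional outcome in hierarchical order. The first rule is "Using the modified Rankin Scale (mRS) with mRS 4–6 indicating a poor outcome (dichotomized"; mRS 6 is death. The fallback reads: "if a mRS score cannot be assigned using the standardized assessment, a poor outcome (yes/no) will be based on whether the patient is dependent". Dependence here refers to basic activities of daily living. Section 2.12.1 carries this into the analysis: "We will evaluate the functional outcome by dichotomizing the modified Rankin scale", with the ADL answer used where the mRS is missing.

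**Missing data.** Section 2.13 says "we anticipate that the proportion of missing values on main dichotomous outcomes will be less than 5" per cent. If missing data cannot validly be ignored, multiple imputation will be considered and best-worst and worst-best scenarios presented. The condition is left to a cited recommendation. The only unconditional sensitivity analysis sets all participants with missing data to alive, or all to dead.

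**The concern.** Missingness in this outcome cannot be unrelated to the outcome. A known death is always classified, as poor. Among participants with known vital status, only survivors can lack a classification, and most survivors have a good outcome on the plan's figures. Leaving them out shrinks the denominator while removing mainly good outcomes. This happens even if data are missing completely at random among survivors.

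The reported proportions with poor outcome are at stake and, if survivor follow-up differs between arms, so is the relative risk. The trial already holds the information that would prevent most of this, because vital status is the primary endpoint. Section 2.13 does not use it for this outcome. The all-alive/all-dead sensitivity analysis does not help a participant who is known to be alive but whose function is unknown.

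**Working it through.** **Inputs (Section 2.10 unless noted)**
- Control mortality: "approximately 60% of the participants will die".
- Experimental mortality: "54.4% of the participants will die in the intervention groups".
- Poor functional outcome: 65% in control and RR 0.90, so 0.90 × 65% = 58.5% in the experimental group.
- 3500 participants, so 1750 per arm in each comparison; two-sided 5% (Section 2.11).
- Missing: under 5% on main dichotomous outcomes (Section 2.13); 1.8% lost on the primary outcome, including withdrawn consent.
- Arm-specific missing rates are not in the document. They are assumptions here.

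**The plan's own figures first**
- 60% against 54.4% with 90% power, pooled variance, no continuity correction: 1639 per arm, 3278 in total, as stated.
- 65% against 58.5% with 1750 per arm: power 97.7%, against the stated 98%.

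**Poor outcome among survivors**, q = (P − d)/(1 − d), with P the poor proportion and d mortality
- Control: (0.65 − 0.60)/0.40 = 0.125.
- Experimental: (0.585 − 0.544)/0.456 = 0.0899.

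**Available-case proportion.** Let m be the share of all participants with no functional outcome, all survivors, missing at random among survivors:

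observed = [d + (1 − d − m)q]/(1 − m)

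*Equal missingness, m = 5%*
- Control: (0.60 + 0.35 × 0.125)/0.95 = 0.64375/0.95 = 67.8%, which is +2.8 points.
- Experimental: (0.544 + 0.406 × 0.0899)/0.95 = 61.1%, which is +2.6 points.
- RR = 0.6111/0.6776 = 0.902, against a true 0.900.

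At m = 2% the control figure is 0.6475/0.98 = 66.1%; at 3% it is 0.64625/0.97 = 66.6%.

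*Some of the missing also lack vital status.* Suppose 1.8 of the 5 points are losses unrelated to outcome and 3.2 are known survivors. Then m = 0.032/0.982 = 0.0326, and control becomes (0.60 + 0.3674 × 0.125)/0.9674 = 66.8%, which is +1.8 points.

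*Unequal missingness, no true effect (60% dead and 65% poor in both arms)*

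| Missing, control / experimental (assumed) | Observed poor | False difference | RR | Approximate two-sided rejection rate |
|---|---|---|---|---|
| 5% / 5% | 67.8% / 67.8% | 0 | 1.000 | 5% |
| 2% / 3% | 66.1% / 66.6% | 0.55 points | 1.008 | 6% |
| 2% / 5% | 66.1% / 67.8% | 1.7 points | 1.026 | 18% |

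The rejection rate is the normal probability of exceeding ±1.96 after a shift of (false difference)/SE, with SE = √[p₁(1 − p₁)/n₁ + p₂(1 − p₂)/n₂] and n = 1750 × (1 − m) in each arm.

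*Unequal missingness, true RR 0.90.* With 2% missing in control and 5% in experimental, RR = 0.6111/0.6607 = 0.925. Reversed, RR = 0.5951/0.6776 = 0.878.

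**How firm is the direction?** If a share r of the missing control survivors is poor, observed = (0.65 − m·r)/(1 − m). At m = 5%:
- r = 0 gives 68.4%
- r = 0.125 gives 67.8%
- r = 0.5 gives 65.8%
- r = 0.65 gives 65.0%

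The direction reverses only if more than 65% of missing survivors are poor.

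**The case against.** The strongest reply has five parts.

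1. **The effect measure is robust to equal missingness.** Section 2.12.2 reports relative risks, and 5% missing in both arms moves the RR by 0.002. This stands. Every materially distorted RR above needs an assumed imbalance between arms.

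2. **Little in the plan suggests an imbalance.** Only the treating team is unblinded; outcome assessors and data managers are blinded (Section 2.3). The interventions end at 36 or at most 72 hours (Sections 2.5 to 2.7), and function is assessed at 6 months. This largely stands: differential follow-up cannot be excluded, but it is not shown to be likely.

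3. **The 5% figure is a ceiling.** In control it means 5/40 = 12.5% of survivors with neither an mRS nor an ADL answer, although the fallback exists to prevent that. Some missing participants may lack vital status too. This stands, and it makes 2.8 points an upper value under the missing-at-random assumption.

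4. **Safeguards exist and name this outcome.** The best-worst and worst-best scenarios in Section 2.13 mention poor functional outcome. With 2% against 5% missing and no true effect they give RR 0.64375/0.6675 = 0.964 and 0.69375/0.6475 = 1.071, which bracket the truth. They are conditional, however, and as extreme bounds they do not correct the main estimate. The cited recommendation is not at hand, so its criterion counts neither for nor against the plan.

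5. **No conclusion rests on this outcome.** Section 2.11 rules out conclusions from secondary outcomes. This stands, so an inflated rejection rate has no decision attached to it.

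A reader might infer that the plan builds a bias into the treatment effect on function, or that overstatement of poor outcome is certain. The document supports neither. The first needs unequal survivor follow-up, and the second needs missing survivors to be poor less often than 65%, which is very likely but not guaranteed.

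**Conclusion.** The point holds as a modest defect in how a secondary outcome is handled. The available-case rule treats known survivors of unknown function as if nothing were known about them, while all known deaths stay in as poor. The reported proportions are then probably too high: by up to about 2.8 points in control at 5% missing, and about 1.8 points if 1.8% of participants are lost for reasons unrelated to outcome. Both figures assume that missing survivors resemble observed ones.

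The RR is essentially unaffected by equal missingness. If follow-up of survivors differs, the false difference under no effect runs from 0.55 points (2% against 3%) to 1.7 points (2% against 5%). Those splits are assumptions; the document gives no arm-specific rates. The primary outcome and the trial's conclusions are not touched. This is an inexpensive improvement and not a demonstrated bias in the treatment comparison.

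**What to change.** In Section 2.13, add a rule for the functional outcome:

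- Participants known to be alive at 6 months but without an mRS or ADL answer stay in the analysis. Their poor or good status is multiply imputed among survivors only, from allocation, site and baseline variables already collected, such as those listed for the subgroup analyses. Known deaths remain poor.
- Participants with unknown vital status follow the general missing-data rule.
- The number and share of survivors without a functional assessment are reported by arm in each of the three comparisons.
- The available-case result and the best-worst and worst-best scenarios are reported as sensitivity analyses.

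The cost is a few sentences in the SAP and one extra imputation model, with no new data. The downside is that the model assumes data are missing at random among survivors given those variables. The best-worst and worst-best scenarios show how far results could move if that fails.

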In SED‐CARE: We estimate a power of 92% to detect a relative risk reduction or increase of 9% for the predefined serious adverse events with 61% of cases in the control group.In TEMP‐CARE: We estimate a power of 92% to detect a relative risk reduction or increase of 9% for the predefined serious adverse events with 63% of cases in the control group.In MAP‐CARE: We estimate a power of 91% to detect a relative risk reduction or increase of 10% for the predefined serious adverse events with 57% of cases in the control group.The anticipated intervention effects in the above‐mentioned sample size and the power estimations correspond to an absolute risk reduction of 5.6%.

We estimate a power of >90% to detect a difference in 5 points on the EQ‐5D‐5L VAS scale, based on a mean value of 75 in the control group and a standard deviation of 20 points.^4^

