#### Assessments of underlying statistical assumptions for linear regression

2.14.2

We will visually inspect quantile–quantile plots of the residuals to assess if the residuals are normally distributed and use residuals plotted against covariates and fitted values to assess for homogeneity of variances.^25^, ^26^ If the plots show deviations from the model assumptions, we will consider transforming the outcome, for example, using log transformation or square root and/or using robust standard errors.^24^, ^25^, ^26^

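### For EQ-VAS, the unbounded mean-plus-two-SDs rule imputes 115 on a 0–100 scale at the plan's own planning values

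*SAP article*

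**What the plan says.** Section 2.12.1 (Outcomes) of the SAP article treats the EQ-VAS "scale as a continuous variable (0–100". Section 2.12.3 analyses it by mixed-effects linear regression and reports group means, SDs and mean differences. It is the only continuous outcome among the primary and secondary outcomes; the exploratory outcomes go to section 2.12.4 as count data.

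Section 2.10 (Sample size and power estimations) plans EQ-VAS "based on a mean value of 75 in the control group and a standard deviation of 20 points", with a target difference of 5 points.

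Section 2.13 (Handling of missing data) provides for multiple imputation and best-worst/worst-best scenarios "if it is not valid to ignore missing data". For continuous outcomes the favourable fill-in is fixed thus: "we will define a beneficial outcome as the group mean plus two SDs of the group mean (fixed imputation". The unfavourable one is "a harmful outcome as the group mean minus two SDs of the group mean (fixed imputation". Neither is limited to the range of the scale.

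Section 2.14.2 covers departures from the linear-model assumptions: "we will consider transforming the outcome, for example, using log transformation or square root and/or using robust standard errors".

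**The concern.** The scenarios are there to show how far the missing values could move the result. A fill-in value above the maximum of the instrument cannot be part of that range. At the planning values this is not an edge case: the ceiling of 100 lies (100 − 75)/20 = 1.25 SDs above the mean, so two SDs must overshoot it. The two scenarios would then show a shift that partly comes from scores that cannot exist, on a scale where the plan's target difference is only 5 points.

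The phrase about SDs of the group mean adds an ambiguity. The usual reading is the SD of the participants' scores. Taken literally, the SD of a mean is its standard error, which would make the bounds very narrow. Section 2.15 has two statisticians working independently, so the phrase should have one meaning.

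A secondary point concerns the transforms named in section 2.14.2. A log is undefined at 0, which is a permitted score, and log and square root reduce right skew, whereas a score with a mean near its ceiling is more likely to be left-skewed.

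**Working it through.** **Inputs.** Mean 75, SD 20, target difference 5, control mortality 60%, intervention mortality 54.4% and total sample 3500 (section 2.10); range 0–100 (section 2.12.1); fill-in values at mean ± 2 SD (section 2.13); two-sided 5% (section 2.11). The missing share m per arm is an assumption: section 2.13 expects less than 5% only for the main dichotomous outcomes and gives no figure for EQ-VAS.

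**1. The plan's own power figure.** The plan states: "We estimate a power of >90% to detect a difference in 5 points".
- By the normal approximation, 90% power needs n = 2 × (1.960 + 1.282)² × (20/5)² ≈ 337 per arm.
- Expected survivors are 1750 × 0.40 = 700 and 1750 × 0.456 = 798, giving 99.8% power. If only half of the survivors respond, power is 92.7%.
- The statement is reproduced, so 75 and 20 are usable inputs.

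**2. Fill-in values as written.**
- Beneficial: 75 + 2 × 20 = 115, which is 15 points above the maximum.
- Harmful: 75 − 2 × 20 = 35, which is on the scale.
- If the intervention mean is 5 points higher: 80 + 40 = 120 and 80 − 40 = 40.

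**3. When the rule stays on the scale.** This needs mean + 2 SD ≤ 100. At mean 75, the SD must be ≤ (100 − 75)/2 = 12.5. At SD 20, the mean must be ≤ 100 − 40 = 60.

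**4. Effect on the best-worst shift.** Take equal observed means of 75 and a missing share m in each arm. The experimental mean becomes 75 + 40m and the control mean 75 − 40m, so the difference moves by m × (115 − 35) = 80m. With the beneficial value capped at 100 it moves by m × (100 − 35) = 65m. The worst-best case is the mirror image.

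| Missing per arm (assumed) | As written (80m) | Capped at 100 (65m) | From impossible values (15m) |
|---|---|---|---|
| 5% | 4.0 | 3.25 | 0.75 |
| 10% | 8.0 | 6.5 | 1.5 |
| 20% | 16.0 | 13.0 | 3.0 |

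The shift reaches 5 points at m = 5/80 = 6.25% as written and at m = 5/65 = 7.7% when capped.

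**5. The standard-error reading.** With 700 survivors, 2 × 20/√700 ≈ 1.5, so the fill-in values would be about 73.5 and 76.5. They stay on the scale but are far too close together for a best or worst case. The two readings differ by a factor of √700 ≈ 26 in the offset (40 against 1.5).

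**6. The transforms.** The documents give no EQ-VAS distribution, so two assumed shapes on 0–100, both with mean 75 and SD 20, were simulated:

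| Assumed shape | Skew, raw | Skew, square root | Skew, log(x + 1) |
|---|---|---|---|
| Beta | −0.88 | −1.32 | −2.01 |
| Truncated normal | −1.03 | −1.67 | −3.08 |

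In both, each named transform makes the left skew worse.

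**The case against.** The strongest reply is that the rule does not exaggerate what could happen. The scale allows fill-in values of 100 and 0, a gap of 100 points, while the rule as written uses 115 and 35, a gap of 80. At 5% missing that is 4.0 points against an attainable 5.0. This stands. A reader might infer that the written rule overstates the possible range and makes a robust result look fragile, but the figures do not support that. What remains is narrower: 15 of the 80 points lie where no score can be.

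It is also fair that the cap seldom changes the reading. At 5%, 10% and 20% missing, both versions fall on the same side of the 5-point target; they part only between 6.25% and 7.7%.

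A reader might extend the point to the analysis in which deaths are scored 0, where mean minus two SDs would be about −48. The plan does not support this. That analysis uses a stratified Wilcoxon test (section 2.12.3), and nothing in section 2.13 applies the fixed fill-in rule to it.

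On the transforms, section 2.14.2 only says they will be considered, as examples, and offers robust standard errors in the same sentence. No one is committed to a log. Only a survivor scoring exactly 0 would break it, and left skew is likely rather than documented. Nor does it follow that a result in EQ-VAS points would be lost, since section 2.12.3 promises mean differences in any case. The transform point is therefore a preference between options the plan already holds.

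Finally, the standard-error reading is strained, because section 2.12.3 speaks of SDs for each group. The phrase should still be cleaned up, since it costs nothing.

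**Conclusion.** The rule is wrong as written for the one outcome it governs among the primary and secondary outcomes. At the planning values it imputes 115 on a 0–100 scale, and it contributes 0.75, 1.5 or 3.0 points of impossible shift at an assumed 5%, 10% or 20% missing per arm. The value 115 rests on the planning mean and SD. The real value will follow the observed data and exceeds 100 whenever mean + 2 SD does. The shifts also assume equal observed means and equal missing shares in the two arms.

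The point is minor. It touches a sensitivity scenario run only if missing data cannot be ignored, for a secondary outcome from which section 2.11 says no conclusions will be drawn. The primary mortality analysis is unaffected. The remark on transforms is secondary and rests on a likely, unproven, left skew.

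**What to change.** In section 2.13, bound the fill-in values for EQ-VAS to the scale: beneficial = min(mean + 2 SD, 100) and harmful = max(mean − 2 SD, 0). Replace the reference to SDs of the group mean with *SDs of the individual values in the group*.

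In section 2.14.2, state that for EQ-VAS robust standard errors are preferred to a log or square-root transform. This keeps the estimate in points, comparable with the 5-point target.

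The cost is SAP wording only: no new data, no change in sample size and no change to the primary analysis. It is best done before the outcome data are analysed.
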